## Abstract

**Background:**

Glaucoma is a chronic progressive optic neuropathy that necessitates lifelong treatment to reduce the decline of the optic nerve. Due to the extended and continuous treatments required for patients, complementary therapies are often considered alongside conventional treatments to enhance the effectiveness of the treatment. Acupuncture has demonstrated the potential to lower intraocular pressure in previous clinical trials, making it a promising glaucoma intervention.

**Objective:**

The primary objective of this study is to conduct a single-center randomized control trial involving patients with glaucoma. Acupuncture will be evaluated as an adjunctive therapy. The trial aims to explore its effectiveness for glaucoma.

**Methods:**

In this single-center randomized controlled trial, participants (N=50) with primary open-angle glaucoma will be randomly assigned to the treatment group, receiving ophthalmic acupuncture with “De Qi” sensation, or the control group, receiving minimum acupuncture stimulation on nonophthalmic acupoints. The intervention will consist of weekly acupuncture treatments for a total of 6 sessions. Participants will be assessed at 8 time points, which are baseline, during the intervention (6 times), and at a 3-month follow-up. The primary outcome measure is a change in the intraocular pressure before and after each acupuncture treatment. Secondary outcomes will include measurements of heart rate and blood pressure before and after acupuncture, best-corrected visual acuity, visual field, optical coherence tomography, optical coherence tomography angiography, the Glaucoma Symptom Scale, and the Glaucoma Quality of Life-15 questionnaire.

**Results:**

Recruitment of participants for the trial commenced on June 28, 2023. A total of 10 participants have been enrolled to test the feasibility of the experiment. We anticipate that the preliminary data from this trial will be completed by December 2025.

**Conclusions:**

This trial uses rigorous methodology and comprehensive outcome measurements to assess the clinical efficacy of acupuncture as an adjunctive therapy for glaucoma, providing valuable insights for future clinical treatment guidelines.

**Trial Registration:**

ClinicalTrials.gov NCT05753137; https://clinicaltrials.gov/study/NCT05753137

**International Registered Report Identifier (IRRID):**

DERR1-10.2196/57888

## Introduction

Glaucoma is a chronic optic nerve disease involving progressive loss of retinal ganglion cells, necessitating long-term treatment with minimal side effects. Some patients may choose to supplement their conventional medical interventions with complementary or alternative medicine [1-3].

In complementary and alternative therapies, there is literature on treating glaucoma with acupuncture, auricular acupressure [4], herbal medicine [5,6], nutritional supplements [7], and Ayurvedic medicine [8]. Possible mechanisms for acupuncture treatment have been proposed, including the release of neurochemical substances through acupuncture stimulation; the influence of acupuncture on ocular blood flow parameters [9,10]; and the upregulation of neurotrophic factors, such as nerve growth factor and brain-derived neurotrophic factor expression in the retina [11]. In an observation study on acupuncture treatment for glaucoma, Law et al [12] conducted a prospective study including 11 patients with glaucoma and observed a short-term increase in intraocular pressure (IOP) after acupuncture [12]. However, another study presented a different perspective, suggesting that acupuncture at the acupoints Jingming (BL1) and Qiuhou (EX-HN7) was beneficial in reducing IOP [13]. Systematic literature reviews have also supported the potential of acupuncture in lowering IOP and improving visual fields [14].

The objective of this single-center randomized control trial is to evaluate the clinical efficacy of acupuncture in the context of glaucoma and provide a reference for future clinical treatment guidelines.

## Methods

### Design and Setting

The study is designed as a single-center, parallel-arm, randomized controlled trial. It will take place in the clinic of China Medical University Hospital. The trial will be conducted from June 2023 until 50 patients finish acupuncture treatment and follow-up assessment. This protocol is reported following the SPIRIT (Standard Protocol Items: Recommendations for Intervention Trials) 2013 statement, which defines standard protocol items for clinical trials [15].

The main purpose of the trial is to investigate the effectiveness of acupuncture in the treatment of glaucoma, including its potential to decrease IOP and reduce optic nerve damage. All participants will be randomly assigned to 2 groups: the treatment group and the control group. Participants in the treatment group will receive acupuncture treatment targeting acupuncture points related to ophthalmology, while participants in the control group will receive minimum acupuncture targeting nonophthalmic acupuncture points.

In addition, all participants will undergo ophthalmic examinations and follow-up. Figure 1 illustrates the enrollment process of the trial. The assessments will include measurements of IOP, heart rate (HR), blood pressure (BP), best-corrected visual acuity (BCVA), central corneal thickness, visual field (VF), optical coherence tomography (OCT) imaging, optical coherence tomography angiography (OCTA), and visual function questionnaire.

**Figure 1 figure1:**
[figure not shown]
The enrollment process of the trial.

### Sample Size Calculation and Power

Assuming an effect size of 0.40 and a type I error (α) of .05, a sample size of 40 people (20 in each group) is required to achieve a statistical power of 95% CI. Assuming a dropout rate of 25%, a total of 50 people (25 in each group) is needed (Textbox 1).

Inclusion and exclusion criteria.

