### Randomization and Allocation Concealment

The participants will be randomly assigned to 2 groups with a 1:1 ratio using random number generation in Microsoft Excel. A computer-based simple random sampling method without stratification with a 1:1 ratio will be used. After the random allocation is completed, the researchers will assign sequential numbers (1-50) to the participants and prepare 50 folders. The appearance of the folders will be identical for both groups, and the section containing the participant’s group and the intervention measures will be sealed. When participants complete the informed consent process, the acupuncturist will unseal the section and begin the acupuncture treatment.

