### Statistical Analysis

The statistical analysis will be performed by a statistician from the [name]’s laboratory who is completely blind to patient allocation, using SPSS software (version 29.0; IBM Corp). The demographic data between the 2 groups, including sex, age, initial IOP, HR and BP, and BCVA will be compared using the 1-tailed Student *t* test. For the data from the 2 glaucoma questionnaires, a 1-way ANOVA will be used. In addition, a repeated measures analysis will be conducted in the trial. The data will be presented as mean (SD), and a *P* value of less than .05 will be considered statistically significant. Subgroup analysis will be conducted based on factors, such as age; gender; changes in IOP before and after treatment; VF, OCT, and OCTA data; and central corneal thickness, among others. In cases of small sample size, the Mann-Whitney *U* test and the Wilcoxon signed-rank test will be used if data do not follow normal distribution. Missing data will be analyzed using pairwise deletion.

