### Conclusions

This study strengthens our understanding of acupuncture as a potential adjunctive therapy for glaucoma, The methodological rigor, including a randomized controlled trial, enhances the credibility of findings. The comprehensive evaluation, incorporating diverse outcome measures such as IOP, cardiovascular parameters, and various ophthalmic assessments, provides valuable insights into acupuncture’s impact on glaucoma management. The 12-week observation period contributes valuable information on both short-term and potential long-term effects.

However, limitations include the single-center design, affecting generalizability, and a modest sample size that may compromise statistical power. The study’s duration may not fully capture long-term effects.

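### The claimed 95% power from 20 people per group at effect size 0.40 cannot be reproduced from the inputs the article states

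*Protocol article*

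**What the plan says.** The protocol article, under Sample Size Calculation and Power, starts from "Assuming an effect size of 0.40 and a type I error (α) of .05" and concludes that "a sample size of 40 people (20 in each group) is required to achieve a statistical power of 95% CI". It then allows for losses: "Assuming a dropout rate of 25%, a total of 50 people (25 in each group) is needed". Allocation is 1:1 in two parallel arms.

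That section does not say whether 0.40 is Cohen's d, Cohen's f or something else. It also does not give the test, its sidedness, the number of readings or a within-person correlation.

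Elsewhere, the Abstract makes the primary outcome the change in intraocular pressure around each of six sessions and lists eight assessment time points. Statistical Analysis announces a repeated measures analysis without tying it to an outcome or to the sample size. Its only mention of sidedness is for baseline characteristics, which "will be compared using the 1-tailed Student *t* test". The Conclusions list as a limitation "a modest sample size that may compromise statistical power".

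**The concern.** The paragraph gives an effect size, an alpha, a group size and a power, and presents the group size as what that power requires. A reader who puts the first three into a standard two-group calculation does not get the fourth, and on the most common reading of an effect size of 0.40 the gap is very large.

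The power figure is what a reader uses to judge how informative a non-significant pressure result would be. As published, the reader cannot tell whether the trial's power is near 23%, 70% or 95%. The wording of the power figure, with CI attached, gives no help in working out what was calculated.

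**Working it through.** **Inputs from the article:** effect size 0.40, alpha .05, 20 per group (N = 40), stated power 95%, dropout 25%, 50 enrolled. **Not stated, so varied here:** metric (d or f), sidedness, number of readings m, within-person correlation ρ.

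**1. Attempt to reproduce the stated figure with a single comparison of 20 versus 20.** Noncentral t with df = 2 × 20 − 2 = 38 and noncentrality δ = d × √(n/2) = d × √10. Critical values are 2.024 (two-sided) and 1.686 (one-sided). With two equal groups, d = 2f.

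| Reading of 0.40 | δ | Power, two-sided | Power, one-sided | n per group for 95% (two-/one-sided) |
|---|---|---|---|---|
| d = 0.40 | 0.40 × 3.162 = 1.265 | 23.4% | 34.4% | 164 / 136 |
| f = 0.40, so d = 0.80 | 0.80 × 3.162 = 2.530 | 69.3% | 79.9% | 42 / 35 |

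Neither reading gives 95%. With 20 per group, 95% power needs d of about 1.17 (two-sided) or 1.06 (one-sided).

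**2. Repeated-measures between-group effect, N = 40.** Noncentral F with 1 and 38 df, equal correlations assumed, λ = f² × N × m / (1 + (m − 1)ρ). For f = 0.40 and m = 6 the numerator is 0.16 × 40 × 6 = 38.4.

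| ρ (assumed) | λ | Power |
|---|---|---|
| 0.30 | 38.4/2.5 = 15.36 | 96.8% |
| 0.36 | 38.4/2.8 = 13.71 | 95.0% |
| 0.50 | 38.4/3.5 = 10.97 | 89.8% |
| 0.70 | 38.4/4.5 = 8.53 | 81.2% |

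The correlation limit moves with m: 95% is reached with three readings up to ρ = 0.20 and with eight readings up to ρ = 0.39. If 0.40 is d (f = 0.20), six readings give 48% at ρ = 0.3 and 30% at ρ = 0.7.

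**3. Group-by-time interaction, N = 40.** Noncentral F with m − 1 and 38(m − 1) df, λ = f² × N × m / (1 − ρ). For f = 0.40, m = 2 and ρ = 0.3, λ = 0.16 × 40 × 2 / 0.7 = 18.29 and power is 98.6%; 32 people in total would give 95%. At ρ = 0, two readings give 93.6%. With six to eight readings and ρ from 0 to 0.5, 10 to 22 people in total give 95%. On this route 40 is generally more than the stated power requires.

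**4. Dropout.** 40 × 1.25 = 50, which is how the article's figure arises. To retain 40 after losing 25%, 40/0.75 = 53.3, so 54 are needed. Enrolling 50 leaves 50 × 0.75 = 37.5, about 37 people or 18 to 19 per group. For a single two-sided comparison of that size:

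| Quantity | 18 per group | 19 per group |
|---|---|---|
| Power at d = 0.40 | 21.5% | 22.4% |
| Power at d = 0.80 | 64.5% | 67.0% |
| d detectable with 80% power | 0.96 | 0.94 |

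At the midway value of 18.75 per group this is about 22%, about 66% and about 0.94.

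**The case against.** The strongest reply is that a single t test is not what the trial plans for its primary outcome. Pressure is measured repeatedly, a repeated measures analysis is announced, and the only t test named is for baseline data. With f = 0.40 and a modest correlation, or with an interaction test, power at N = 40 does reach or pass 95%. Other routes get there too. Baseline adjustment with d = 0.40 gives 98% if the baseline correlation is 0.95, and 0.40 read as f² in a one-predictor regression gives 97%, though 35 people would then suffice. This stands: the 95% cannot be called wrong outright, and the 23% should not be presented as the trial's power, because it assumes d and a two-sided single comparison, neither of which is stated.

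What the reply does not do is rescue the sentence. Each route depends on a metric, test or correlation that the sample size section does not give, and different choices move the answer from about 23% to nearly 100%. Nor is this merely detail that an article leaves to a fuller document: the article publishes a specific number, and its printed inputs do not lead to it.

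Two stronger readings are tempting. A reader might infer that a null result will be taken as proof of no effect. No section plans that reading, and the Conclusions caution about power. A reader might also infer that the Conclusions contradict the 95% claim. That remark is a general limitation set beside single-center design and duration, not a competing power figure. It sits awkwardly with 95% but does not refute it.

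**Conclusion.** The point holds as a failure to reproduce, not as proof of an underpowered trial. With 20 people per group, alpha .05 and one between-group comparison, power is 23% or 34% (two- or one-sided) if 0.40 is d, and 69% or 80% if it is f. Reaching about 95% takes further assumptions that are not on the page, and the interaction route that passes it generally makes 40 more than is required. These results rest on normally distributed outcomes with equal variances, on people as the unit of analysis and, for the repeated-measures figures, on equal correlations whose values are assumed here.

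Separately, the article's own dropout assumption leaves about 37 completers rather than 40, which lowers power a little further on every reading.

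**What to change.** Keep 50 participants and rewrite the paragraph. Delete CI after the power figure. State whether 0.40 is d or f, which test on which outcome was powered, its sidedness and, for a repeated-measures test, the number of readings and the assumed correlation. Then give the power that follows, based on the 18 to 19 completers per group that 25% dropout leaves, and correct the inflation statement: 50 is 40 × 1.25, whereas retaining 40 would take 54.

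If a single two-sided between-group comparison is meant, the text could say that about 19 completers per group give 80% power for d of about 0.94, with about 22% for d = 0.40 or about 66% for d = 0.80, depending on which metric was intended. If a repeated-measures test is meant, quote its power over a plausible range of correlations rather than at one value.

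The cost is one reworded paragraph and no extra patients. The drawback is that the stated power will probably be less favourable.

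### The dropout inflation multiplies by 1.25 instead of dividing by 0.75, so 50 randomized do not leave the required 40 at 25% loss; the end-of-trial rule separately treats 50 as finishers

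*Protocol article*

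**What the plan says.** Sample Size Calculation and Power sets the base requirement in two steps. The inputs are "Assuming an effect size of 0.40 and a type I error (α) of .05", and the result is that "a sample size of 40 people (20 in each group) is required to achieve a statistical power of 95% CI". I read the last words as 95% power. The section then allows for losses: "Assuming a dropout rate of 25%, a total of 50 people (25 in each group) is needed".

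Three places treat 50 as the number randomized. The sample size section presents it as the total after allowing for dropout. The Abstract (Methods) says that "participants (N=50) with primary open-angle glaucoma will be randomly assigned to the treatment group". Randomization and Allocation Concealment has the researchers "assign sequential numbers (1-50) to the participants and prepare 50 folders".

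Design and Setting uses the same number differently: "The trial will be conducted from June 2023 until 50 patients finish acupuncture treatment and follow-up assessment". Here 50 counts the people who complete treatment and follow-up.

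**The concern.** There are two separate problems.

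The first is arithmetic. A dropout rate applies to those who enter the trial, so the number to enter is the number needed at the end divided by the fraction retained. Adding 25% of the final number to itself is a different operation and gives too small a total. On its own assumption, the trial would then expect fewer completers than the number it calls required.

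The second is a contradiction about what 50 means. One rule closes recruitment at 50 randomized. The other keeps the trial open until 50 have finished. Since the article assumes that a quarter will drop out, the two rules stop at different points, and only 50 allocations have been prepared.

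At stake are a correct statement of what the trial can deliver and a single, unambiguous stopping point for enrolment.

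**Working it through.** **Inputs.** Required at the end: 40 in total, 20 per group. Dropout: 25%. Stated total: 50, 25 per group (all from Sample Size Calculation and Power). Allocations prepared: 50 (Randomization and Allocation Concealment). End-of-trial rule: 50 finishers (Design and Setting). I take the 40 as given.

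**Reproducing the stated figure.** 40 × (1 + 0.25) = 50, and per group 20 × 1.25 = 25. This matches the article exactly, so multiplication by 1.25 is evidently how the figure was obtained.

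**Correct inflation.** n/(1 − d) = 40/0.75 = 53.3, rounded up to 54. Per group, 20/0.75 = 26.7, rounded up to 27. The stated total is 4 below this.

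**What 50 delivers.**
- At 25% dropout: 50 × 0.75 = 37.5, so 37 to 38 completers; per group 25 × 0.75 = 18.75, so 18 to 19. The shortfall against 40 is 2 to 3 people.
- Dropout at which 50 leaves exactly 40: 1 − 40/50 = 20%.
- If each of 50 people completes independently with probability 0.75, the binomial chance of at least 40 completers is 0.26. With 25 per group, the chance of at least 20 in a given group is 0.378, and in both groups 0.378² = 0.14.

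**Effect on power.** Suppose 40 gives 95% power at two-sided 5%. The implied noncentrality is 1.960 + 1.645 = 3.605. With 37.5 it becomes 3.605 × √(37.5/40) = 3.49, and power is Φ(3.49 − 1.96) = Φ(1.53) = 0.937, about 94%. The standard error rises by √(40/37.5) − 1 = 3%.

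This is conditional on the 95%. The article does not say which effect-size measure or test the 0.40 belongs to, so the base figure of 40 cannot be confirmed from it.

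**The two meanings of 50.**

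| Reading | Randomized | Finishing at 25% dropout |
|---|---|---|
| 50 randomized (Abstract, sample size section, folders) | 50 | 37.5 |
| 50 finish (Design and Setting) | 50/0.75 = 66.7, so 67 | 50 |

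The second reading needs 67 − 50 = 17 allocations beyond those prepared (18 if the groups are to be equal, at 68). The readings coincide only at zero dropout.

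**The case against.** The strongest reply is that little depends on this. The shortfall is 2 to 3 people, the loss of power is about one percentage point if the base calculation is sound, and the Conclusions already concede that the modest sample may limit power. The primary outcome is recorded before and after every session, so many people who drop out would still contribute primary data; 37.5 full completers is therefore not the number behind the primary comparison. All of that stands, and it limits the severity. It does not make the arithmetic right or remove the conflict over what 50 means.

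Three stronger inferences are tempting, and the article does not support them.

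- **That the two problems add up.** They are alternatives. If 50 really finish, the target of 40 is exceeded, and it is the recruitment total and folder count that are wrong. If 50 are randomized, the figure of 67 does not arise.
- **That dropouts will be replaced, or only completers analysed.** No section mentions replacement. Ethical Considerations says that the data available from patients who withdraw will be used in the final analysis, and the pairwise deletion in Statistical Analysis also keeps partial records. The end-of-trial sentence reads as a statement of duration, not as the definition of an analysis set.
- **That the randomization cannot give 25 per group.** The article says that "A computer-based simple random sampling method without stratification with a 1:1 ratio will be used". If this means unrestricted allocation, an exact 25:25 split has a probability of only 0.11. But drawing 25 of the 50 numbers at random also fits the words, and it gives 25:25 exactly. Even under the first reading the cost is small: a 20:30 split raises the standard error by √[(1/20 + 1/30)/(2/25)] − 1 = 2%, and 18:32 by 4%. Simple randomization is a valid method, and a request for blocks would be a preference, not a correction.

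**Conclusion.** Both problems hold. The dropout adjustment is wrong as written: 50 comes from multiplying by 1.25, while the article's own requirement and dropout rate call for 54. That conclusion uses only the article's 40 and 25% and does not depend on how the 40 was derived. The statement that the trial runs until 50 finish also contradicts the three places where 50 is the number randomized.

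The size is modest: 37 to 38 expected completers against 40, and power of about 94% in place of 95%. The power figure assumes that 40 truly gives 95% with a two-sided 5% test, which cannot be checked. The probabilities of 0.26 and 0.14 assume independent dropout, and the 0.14 also assumes 25 per group. This should be corrected, because a stated sample size and a stated end-of-trial rule are wrong or in conflict. It does not undermine the design.

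**What to change.** 1. **Sample Size Calculation and Power.** Keep 50 and the 25% dropout assumption, and state that 37 to 38 completers (18 to 19 per group) are expected, with the slightly lower power that follows. Quote about 94% only once the effect-size measure and test behind the 40 have been stated and the 95% confirmed. Alternatively, state that 50 randomized secures 40 completers only if dropout does not exceed 20%. This should be worded as a limit on what 50 covers, because the article gives no evidence for a 20% rate. Raising enrolment to 54 would also settle the arithmetic, at the cost of four more participants and four more allocations, but the shortfall is too small to make that necessary.

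2. **Design and Setting.** Reword the end-of-trial sentence so that the trial ends when 50 participants have been randomized and the last of them has passed the week-12 assessment. This agrees with the Abstract, the sample size section and the 50 folders.

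Apart from the optional increase to 54, both changes are wording only. They need no new participants, no new folders and no change to the allocation procedure already in use for the 10 people enrolled when the article was written.
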